## Abstract

**Introduction:**

Complete recovery after surgery depends on psychological factors such as preoperative information, expectations, and surgery-associated anxiety. Prior studies have shown that even a short preoperative psychological intervention aiming at optimized expectations (EXPECT) can improve postoperative outcomes in coronary artery bypass patients. However, this intervention may benefit only a small subgroup of heart surgery patients since implementing preoperative psychological interventions into the daily clinical routine is difficult due to the additional time and appointments. It is unclear whether the EXPECT intervention can be shortened and whether heart valve patients would also benefit from interventions that optimize patients’ expectations. The multicenter ValvEx trial aims (i) to adapt an effective preoperative psychological intervention (EXPECT) to make it brief enough to be easily integrated into the preoperative routine of heart valve patients and (ii) to examine if the adapted preoperative psychological intervention improves the subjectively perceived illness-related disability (PDI) up to 3 months after surgery.

**Materials and analysis:**

In two German university hospitals, *N* = 88 heart valve patients who undergo heart surgery are randomized into two groups [standard of care (SOC) vs. standard of care plus interventional expectation manipulation (SOC and EXPECT)] after baseline assessment. Patients in the EXPECT group additionally to standard of care participate in the preoperative psychological intervention (30–40 min), focusing on optimizing expectations and have two booster-telephone calls (4 and 8 weeks after the surgery, approx. 15 min). Both groups have assessments again on the evening before the surgery, 4 to 6 days, and 3 months after the surgery.

**Discussion:**

The trial demonstrates excellent feasibility in the clinical routine and a high interest by the patients.

**Ethics and dissemination:**

The Ethics Committees of the Department of Medicine of the Philipps University of Marburg and the Department of Medicine of the University of Giessen approved the study protocol. Study results will be published in peer-reviewed journals and presented at congresses.

**Clinical trial registration:**

ClinicalTrials.gov, identifier NCT04502121.

## Introduction

Heart disease accounts for nearly 10% of all recorded diagnoses in Germany, with an upward trend (1, 2). Cardiovascular diseases are prevalent globally, with a point prevalence of 523 million cases recorded in 2019, and are the leading cause of death worldwide (1, 3). The number of cardiovascular surgeries is also steadily increasing: Between 2008 and 2018, there has been an increase of 23% (4). In 2019, 36 650 heart valve surgeries were performed in Germany (2). The aim of surgical heart valve intervention, such as aortic or mitral valve surgery, is to recover the function of the heart valve through reconstruction or replacement (5). Valve surgeries significantly improve the odds of survival for affected patients (5, 6). However, despite high survival rates after cardiac surgery, the postoperative recovery is highly variable and often unfavorable: a substantial number of patients still feel restricted after surgery, still experience a high illness-related disability, do not perceive an improvement in quality of life, suffer pain or have increased depression scores that persist or even rise for weeks and months after hospital discharge (6–14).

Besides the surgical trauma itself and physical factors like age or general health condition, preoperative psychological factors also influence the recovery process after cardiac surgery (6). Preoperative expectations, illness beliefs (e.g., preoperative illness and treatment-related beliefs), anxiety, and depressive symptoms influence the recovery process, chances of survival, perceived physical and psychological disability, perceived quality of life, and depressive symptoms after cardiac surgery (13, 15–21). Negative expectations before coronary surgery, such as expectations regarding the outcome, the consequences, and the success of treatment, lead to more complications, worse quality of life, higher illness-related disability, increased depressive symptoms, and a postponed return to work (13, 22–24). Given the impact of expectations and illness beliefs on postoperative outcomes and the possibility that these constructs are specifically modifiable through psychological preparation, there is a need to develop preoperative interventions to improve long-term recovery (12, 25).

In the context of the PSY-HEART trial, Rief and colleagues addressed this issue and developed a preoperative intervention (EXPECT) to optimize the patients’ expectations before undergoing coronary artery bypass graft (CABG) surgery (21, 26).

Medical treatments combine both specific factors (e.g., active pharmacological ingredient of a drug or a surgical procedure) and unspecific factors (e.g., patients’ expectations of the treatment outcome), while the unspecific factors of treatments are considered crucial for placebo effects. The EXPECT intervention was based on expectations as one of the most important placebo mechanisms driving placebo effects (27). Placebo effects not only influence subjective dimensions (e.g., quality of life) but have been shown to contribute substantially to surgery outcomes and immune parameters (28). The PSY-HEART-trial indicated effects of the intervention on expectations and depressive symptoms: Patients in the intervention group developed higher personal control expectations, more realistic expectations of the duration of disease, and, in some cases, more positive disability expectations compared with standard of care (SOC) (29). The EXPECT intervention consisted of five appointments: two in-person sessions (approx. 40–60 min) and two telephone calls (approx. 15–20 min) 3–10 days before surgery and one booster telephone call 6 weeks after CABG surgery (30). The positive-realistic expectations developed in the intervention were associated with a better course of treatment 6 months after surgery: The results showed a lower illness-related disability [Cohen’s *d* = 0.75; interpretation of the effect sizes: Cohen’s *d*_small effect size_ = 0.2, Cohen’s *d*_medium effect size_ = 0.5, Cohen’s *d*_large effect size_ = 0.8 (31)], a shorter hospital stay (Cohen’s *d* = 0.46), an earlier return to work (Cohen’s *d* = 0.42), and a higher quality of life (Cohen’s *d* = 0.50) (21, 32). The intervention also influenced physiological parameters such as stress/adrenaline (Cohen’s *d* = 0.34) and immunological parameters (Cohen’s *d*_interleukin–8_ = 0.47, Cohen’s *d*_interleukin–6_ = 0.37) positively (21, 33, 34). However, in the PSY-HEART I trial, almost half of the eligible patients (*n* = 99, 44%) declined to participate in the trial because of difficulties traveling to the additional study appointments, additional time required (four measurement time points and if applicable, approx. 140 min for the intervention), or lack of interest. The additional prehospital intervention appointments and time investment hindered patients’ participation in the trial.

A shortened preoperative psychological intervention at hospital admission could offer more patients accessibility to a preoperative psychological intervention (e.g., by reducing the number of appointments before hospital admission and the associated traveling issues). Another advantage could be that a shorter preoperative psychological intervention would fit better into the current daily hospital routine.

Patients undergoing CABG surgery and patients undergoing heart valve surgery do not differ in the recovery process concerning their anxiety and depression scores (35). Heart valve patients benefit from psychological support (35). This raises the question of whether heart valve patients would also benefit from a preoperative psychological intervention to optimize their expectations. Previous research indicates that heart valve patients would like to receive more information about the psychosocial aspects of their disease and the benefits and risks of treatment options (36). Especially because measures such as health-related quality of life are continuously gaining more relevance, a preoperative psychological intervention enhancing the post-interventional quality of life seems to be a promising approach for patients undergoing heart valve surgery, too (37).

Following the encouraging results of the PSY-HEART I trial (which focused on CABG patients), the ValvEx trial (“Preoperative optimization of cardiac **val**ve patients’ **ex**pectations”) now investigates the efficacy of the EXPECT intervention in patients with planned heart valve surgery compared to a control group (Standard of Care, SOC). To address the problems of the EXPECT intervention in the PSY-HEART I trial (total intervention length and amount of additional contacts), the intervention was modified. It was shortened to make it more suitable for the clinical routine and to minimize the additional effort for the patients (no additional appointments and journeys, less time request; total intervention duration of the EXPECT intervention in the PSY-HEART trial: approx. 140 min; total intervention duration of the EXPECT intervention in the ValvEx trial: approx. 70 min).

If this trial can demonstrate that the expectation intervention (EXPECT) is helpful for heart valve patients, the long-term goal is to implement an interventional treatment protocol for heart valve patients to optimize their expectations in clinical routine care.

## Materials and analysis

### Registration and funding

The trial has been pre-registered at http://www.clinicaltrials.gov (NCT04502121). It is funded by the German Heart Foundation (“Deutsche Stiftung für Herzforschung”) (F/41/20 PI [name]). Table 1 contains all items of the World Health Organization Trial Registration Data Set.

**TABLE 1 T1:** World Health Organization trial registration data set.

Items	Information
Primary registry and trial identifying number	ClinicalTrials.gov, NCT04502121.
Date of registration in primary registry	August 6, 2020.
Secondary identifying numbers	F/41/20 (German Heart Foundation).
Source(s) of monetary or material support	German Heart Foundation (“Deutsche Stiftung für Herzforschung”).
Primary sponsor	Division of Clinical Psychology and Psychotherapy, Philipps University of Marburg, Marburg, Germany.
Secondary sponsor(s)	Department for Cardiovascular Surgery, Heart Center, Philipps University of Marburg, Marburg, Germany; Department for Cardiovascular Surgery, Justus-Liebig-University, Giessen, Germany. German Heart Foundation (“Deutsche Stiftung für Herzforschung”).
Contact for public queries	[name], Philipps University of Marburg, Division of Clinical Psychology and Psychotherapy, [name], Germany; [contact]; [contact]; e-mail address: [contact].
Contact for scientific queries	[name]. Philipps University of Marburg, Division of Clinical Psychology and Psychotherapy, [name], Germany; [contact]; [contact]; e-mail address: [contact].
Public title	Optimization of patient expectations to improve outcomes in patients undergoing heart valve surgery.
Scientific title	Preoperative Optimization of Cardiac Valve Patients’ Expectations (ValvEx).
Countries of recruitment	Germany.
Health condition(s) or problem(s) studied	Heart valve patients.
Intervention(s)	Intervention name: EXPECT. Intervention description: preoperative psychological intervention with the aim of optimizing expectations.
	Control group: Standard of care (SOC), no treatment.
Key inclusion and exclusion criteria	Ages eligible for study: ≥ 18 years. Sexes eligible for study: both. Accepts healthy volunteers: no.
	Inclusion criteria: scheduled surgery of aortic valve and/or mitral-valve (minimally invasive or open heart surgery).
	Exclusion criteria: emergency surgery, transcatheter aortic valve implantation (TAVI) procedure.
Study type	Interventional.
	Method of allocation: randomized.
	Masking: medical staff.
	Assignment: two-arm.
	Randomization: balanced block randomization (8:8); prestratifications: study center (Marburg or Giessen); and scheduled type of surgery (minimally invasive or open heart surgery).
	Primary purpose: improvement of the recovery process afer heart valve surgery.
Date of first enrolment	June 2020.
Target sample size	88.
Recruitment status	Recruiting.
Primary outcome(s)	Illness-related disability 3 months after surgery.
Key secondary outcomes	Health-related quality of life, expectations, illness beliefs, anxiety, depression, rehospitalization, length of hospital stay.
Ethics review	Status: Approved.
	1. Ethics Committee of the Department of Medicine of the Philipps University of Marburg (AZ 46/20; 2020-05-20).
	2. Ethics Committee of the Department of Medicine of the University of Giessen (AZ 131/20; 2020-08-17).
Completion date	Remaining.
Summary results	Remaining.
IPD sharing statement	Data can be requested on demand.

World Health Organization trial registration data set version 1.3.1.

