### Recruitment and enrollment

Recruitment began at the end of July 2020. Due to the COVID-19 pandemic, elective surgeries were suspended in the meantime, complicating recruitment, which is currently ongoing. The anticipated termination of the trial is at the end of March 2023. Since the trial begins only upon admission to the hospital and no intervention appointments are scheduled before that time, no changes in implementation were necessary during the COVID-19 pandemic. Cardiac valve patients on waiting lists in heart surgery centers are screened. To generate generalizable outcomes and consider the internal validity simultaneously, the following in- and exclusion criteria were created:

Inclusion criteria are:

•Scheduled surgery of aortic valve and/or mitral valve (minimally invasive or open heart surgery),•Age ≥ 18 years,•Fluency in German and•Capability to informed consent.

Exclusion criteria are:

•Comorbid medical/psychiatric condition that causes more extensive disability than the coronary condition,•Participation in other studies, e.g., PSY-HEART II; in agreement with the coordinating investigator, a patient can participate in cardiovascular studies if this does not interfere with the main study,•Emergency surgery and•Transcatheter aortic valve implantation (TAVI) procedure.

Cardiac valve patients on waiting lists of the heart surgery centers in Marburg and Gießen who fulfill the inclusion criteria receive an information brochure about the study with their standard letter confirming the surgery date via post. Patients interested in participating in the study contact the study coordinators by phone or by a response letter. In a first telephone call, the study coordinators answer questions and schedule the study participation for interested patients on the day of their hospital admission. The patient information is sent home to interested patients so they can read it at their own pace. On the day of admission, a physician or a psychologist talk about the patient information with each patient, and patients will have an opportunity to ask questions about the study before providing verbal and written consent to the study.

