### Random allocation

After baseline assessment, the patients are randomized to the intervention group (EXPECT) or the control group (SOC). Therefore, the interventionist opens a prepared, concealed envelope to allocate a patient. The randomization result was prepared in this envelope by a student assistant who was not involved in the study. The interventionists and the patients do not know the randomization result before the envelope is unclosed. Randomization was done as block randomization with a balanced allocation ratio (1:1) using WINPEPI (56). Two prestratifications were considered: The study center (Marburg or Giessen) and the scheduled type of surgery (minimally invasive or open heart surgery).

The interventionists will inform the patients about the group they are randomly assigned to. The medical staff will not receive any information about the group a patient is allocated to and therefore be blind regarding group assignments. The intervention group receives a preoperative psychological intervention to optimize expectations and standard of care. The control group receives the standard of care only.

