**FIGURE 2 F2:**
[figure not shown]
Intervention schedule for EXPECT [adapted from Laferton et al. (26), Salzmann et al. (57)].

The EXPECT intervention is performed by one of four trained psychology students shortly before graduating based on an intervention manual. The same person conducts the entire intervention of one patient. The intervention sessions are videotaped and supervised for verification of manual fidelity. Each patient in the intervention group receives a booklet with information material and worksheets to remember discussed contents.

Content and procedure are based on the EXPECT intervention of the PSY-HEART I-trial [for more details, please see Rief et al. (21), Laferton et al. (26), Salzmann et al. (30)]. The intervention deals with optimizing individual expectations relating to the surgery and the recovery process since the optimization of positive, realistic expectations as part of placebo effects is expected to improve the recovery process in patients undergoing valvular surgeries. Since expectations have been shown to be a central characteristic of depressive and anxiety symptoms and mental disorders (27), the development and amplification of positive-realistic expectations as well as the correction of dysfunctional expectations and illness beliefs within the intervention should also influence psychological factors such as levels of anxiety or depressive symptoms.

Based on the integrative model of expectations in patients undergoing medical treatment (58), generalized self-efficacy, treatment outcome expectations (benefit expectations), timeline expectations, and personalized outcome expectancy are addressed in the EXPECT intervention. Optimization of expectancy effects refers to two main objectives: First, to optimize positive expectations regarding treatment success and impairment after medical heart valve surgery. Second, the intervention should specifically promote positive expectations about one’s coping skills in case of ordinary but unpleasant concomitant effects and potential aversive events due to the surgical procedure. By optimizing the expectations before surgery, the treatment success and recovery process should be improved.

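### A single printed block layout (8:8) in four strata, with unblinded interventionists opening the envelopes, leaves about 7 of 88 assignments knowable in advance (about 13 to 15 if the block is 8)

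*Protocol article*

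**What the plan says.** The randomisation entry in Table 1 (Registration and funding) reads "Randomization: balanced block randomization (8:8); prestratifications: study center (Marburg or Giessen); and scheduled type of surgery (minimally invasive or open heart surgery". The same table gives the recruitment status as recruiting and lists only medical staff as masked. The Random allocation section adds "Randomization was done as block randomization with a balanced allocation ratio (1:1) using WINPEPI" and names the same two stratification factors.

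On procedure, that section says that a student assistant outside the study prepared the envelopes and that allocation follows the baseline assessment. It continues: "Therefore, the interventionist opens a prepared, concealed envelope to allocate a patient". It then says "The interventionists will inform the patients about the group they are randomly assigned to". It also asserts that neither interventionists nor patients know the result before the envelope is opened.

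Under Psychological intervention, EXPECT is "performed by one of four trained psychology students shortly before graduating". Under Recruitment and enrollment, the consent conversation is described as follows: "On the day of admission, a physician or a psychologist talk about the patient information with each patient". The article mentions no variation in block length.

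**The concern.** In a permuted block, once one arm is used up, every remaining place in that block is determined. A concealed envelope does not protect those places from someone who has counted the earlier ones. Three features make counting feasible here: the layout is in print, each stratum is a short separate sequence, and the people who see the assignments are a group of four. Allocating after baseline does not close the gap, because the count exists before the next patient is consented or assessed.

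Patients know their arm and the primary outcome is a self-reported disability score. If someone with foreknowledge could influence who is encouraged to take part, or how the baseline session is run, the arms could differ for reasons other than the intervention.

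**Working it through.** The plan gives no figure for predictability, so there is none to reproduce.

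**Inputs**
- Layout 8:8 (Table 1). The natural reading is m = 8 per arm, a block of 16. A block of 8 (m = 4) cannot be excluded and is run as the alternative.
- Strata: 2 centres × 2 scheduled surgery types = 4 (Random allocation).
- Target 88 (Sample size and study power), so 88/4 = 22 per stratum on average. Stratum sizes are not given; an equal split is an assumption.
- Constant block length: inferred from the single printed layout.
- The observer knows the layout and all earlier openings in the stratum: an assumption.

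**One completed block, m per arm**
- Expected assignments known with certainty = 2m/(m+1). For m = 8: 16/9 = 1.78 of 16 (11.1%). For m = 4: 8/5 = 1.6 of 8 (20%).
- Probability that at least the last k are known = 2·C(2m−k, m)/C(2m, m). For m = 8: 1 for k = 1, 0.47 for k = 2, 0.20 for k = 3.
- Expected correct best guesses = m + (2^(2m)/C(2m, m) − 1)/2. For m = 8: 10.05 of 16 (62.8%). For m = 4: 5.33 of 8 (66.6%).

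**Whole trial, 22 per stratum**
- Blocks of 16: one block completes per stratum. The other 6 patients cannot exhaust an arm of 8. So 4 × 1.78 = 7.1 of 88 (8%). Simulation agrees (7.1), with best-guess accuracy of about 60.4%. Stratum splits of 32/24/20/12 and 40/24/16/8 also give about 7.
- Blocks of 8: two blocks complete per stratum (2 × 1.6 = 3.2), and the 6 patients of the third add 0.17 on average. So 4 × 3.37 = 13.5 of 88 (15%), with accuracy of about 65%. Letting stratum sizes vary at random gives 15.2. The most uneven split tried gives 17.6.

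**Randomly varying lengths, set of lengths known to the observer, 22 per stratum (simulation)**

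| Lengths | Certain, of 88 | Best-guess accuracy |
|---|---|---|
| Fixed 16 | 7.1 | 60.4% |
| Fixed 8 | 13.5 | 65% |
| 6/8/10/12 | about 1 | about 64.5% |
| 12/16/20 | about 1.2 | about 60.7% |

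Varying the length removes the certain predictions. It does not reduce general guessability, and lengths shorter than the present block increase it.

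**Rough size of a worst case.** Suppose all 7 certain patients were steered in the favourable direction by 0.25 to 0.5 SD (an assumption). With 44 per arm, the arm difference moves by 7 × 0.25/44 = 0.04 to 7 × 0.5/44 = 0.08 SD before baseline adjustment, against a planning effect of d = 0.3. With 13.5 patients it is 0.08 to 0.15 SD. This counts only the certain predictions.

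**The case against.** The strongest reply is that the article shows no one who has both foreknowledge and control over entry. Eligible patients receive a brochure by post and contact the coordinators themselves. Participation is tied to the day of admission for surgery. Consent is discussed by a physician or a psychologist, medical staff are blind, and nothing says that the interventionists screen or obtain consent. Four interventionists across two centres would need a running tally per stratum, and no section describes one. Participation is reported at 77.36% of patients approached, which limits selective enrolment. The primary model adjusts for baseline and would absorb part of any selection on baseline disability.

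All of this stands, and it limits the consequence. A reader might infer that enrolment was steered, that the result is biased, or that a fifth of assignments are exposed. The article supports none of these. The 20% figure is for completed blocks under the less natural reading, and no bias has been demonstrated.

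It can also be said that a constant length is only inferred and that block details belong in a fuller protocol. That is fair for envelope numbering or opacity, which are not raised here. The layout, however, is stated rather than omitted, and it sits beside an assurance that it cannot secure.

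**Conclusion.** The point holds in limited form. If the printed layout is applied throughout, the last place in every completed block follows from the earlier ones, so the concealment statement is not guaranteed for about 7 of 88 patients (blocks of 16), or about 13 to 15 (blocks of 8). This assumes about 22 patients per stratum and an observer who knows the layout and keeps a tally. The finding is that foreknowledge is possible, not that it was used. The likely bias is modest. This is an inexpensive improvement to concealment in a trial with unblinded patients and a subjective endpoint; it does not invalidate the design.

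**What to change.** For patients not yet randomised, the uninvolved assistant should prepare new envelopes at 1:1 within the same four strata. Block lengths should vary at random and be no shorter on average than the present block: for example 12, 16 and 20 if the present block is 16. Lengths of 6, 8, 10 and 12 suit only a present block of 8; against blocks of 16 they would raise best-guess accuracy from about 60% to about 65%. The lengths should be withheld from interventionists and coordinators until the last patient is randomised, and the protocol should say only that they vary. The printed 8:8 then no longer describes future allocations.

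Over a full trial, certain predictions fall to about 1 of 88 and best-guess accuracy stays at about 60–61%. The actual gain depends on how many patients remain, which the article does not state.

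The cost is a new list, refilled envelopes and a short amendment agreed with both ethics committees. No extra patients, visits or staff are needed. The downsides are a possible slight arm imbalance from unfinished blocks, including those abandoned at the switch, and no correction for patients already randomised.
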